##### Randomisation

From the eligible higher-primary school-list obtained from the education department of Srinivaspura taluka, eight schools will be *randomly selected* using computer-generated random-number by an independent researcher. The selected schools will then be assigned to the intervention, and waitlist-control condition (receiving intervention after the post-assessment in intervention-group) by the independent researcher through the *random-allocation* sequence. To ensure allocation concealment, randomly selected schools will be assigned unique study numbers that will not be known to the independent researcher at the central office. The sequence will be delivered through sealed, opaque envelopes.

The selected-schools will be invited to participate in the study, and briefing-meetings will be conducted to inform principals of selected-schools regarding the study. Information on any initiatives/activities related to target outcomes in the selected-schools will be obtained. Local consortium and local stakeholders for education will be interacted to ensure minimal refusal of the selected schools. In case of refusal, the refusing school will be replaced with another school from the eligible school-list. A due care will be taken to prevent possible contamination so that no control-schools will be selected within 5 km radius of intervention-schools. An alternate covariate-constrained randomisation will be considered only if we do not reach an acceptable baseline balance through simple-randomisation.

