##### Intervention-schools

For the schools randomised to the intervention arm, the teachers nominated by their designated superior officials will be trained on the curriculum resource guide content in a 3-day workshop. The teachers who provide consent to participate in the research, complete the training, stay in the selected-schools for the study period and deliver the intervention will be selected. Following baseline assessment of participating students, the trained teachers will then proceed with the implementation of SUMS Intervention Curriculum Resource Guide, which requires approximately 10–15 h of classroom time over two months. In the intervention delivery, the teachers will be given pedagogical flexibility but will be instructed to adhere to the standardised core content, recommended lesson plans and procedures to maintain fidelity (Table 2). Booster sessions will be provided at 2-months and 5-months following the initial intervention.

**Table 2 Tab2:** Quality assurance and data management

**Field-team:** The field-team will comprise of Project-Assistant who will be trained in standard protocols of questionnaire administration for data collection, coordinate with local stakeholders, monitor compliance of intervention protocol and its deviations and also conduct public-engagement activities.	
**Post-recruitment retention strategies:** For the Project-Assistant, all the activities required to achieve the trial goals will be communicated clearly. A weekly meeting will be held to sort out the field related issues. In addition, the teachers, principals, and other key stakeholders will be informed on the trial’s status and progress through newsletters.	

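### Schools are allocated, as written, before agreement, replacement and the 5-km check, so the comparison is not protected as randomised

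*Protocol article*

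**What the plan says.** All the rules on schools stand in Randomisation, in this order.

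- Eight schools are drawn at random from the eligible list.
- "The selected schools will then be assigned to the intervention, and waitlist-control condition". On concealment: "The sequence will be delivered through sealed, opaque envelopes". The time of opening is not given.
- The next paragraph turns to recruitment of schools: "The selected-schools will be invited to participate in the study, and briefing-meetings will be conducted to inform principals of selected-schools regarding the study".
- For refusers: "In case of refusal, the refusing school will be replaced with another school from the eligible school-list". The first eight are expressly random draws. Nothing comparable is said of a substitute, and its arm is not stated.
- Against contamination: "no control-schools will be selected within 5 km radius of intervention-schools".
- As a fallback: "An alternate covariate-constrained randomisation will be considered only if we do not reach an acceptable baseline balance through simple-randomisation".

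Intervention-schools describes a 3-day workshop for teachers in schools already randomised to the intervention, and then: "Following baseline assessment of participating students, the trained teachers will then proceed with the implementation". Blinding makes the trial open-label; only the statistician is blinded. Exclusion criteria removes pupils without assent or parental consent and pupils missing at baseline after two visits. Sample size and power sets 4 schools per arm and 50 pupils per school.

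**The concern.** A cluster trial is protected when the set of schools, and preferably the set of pupils, is fixed before anyone knows the arms. The written order here leaves three openings.

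1. **Refusal after allocation.** The arms ask different things of a school. Intervention schools release teachers for a 3-day workshop and give 10–15 h of class time; control schools wait until after the 12-month assessment. If principals know their arm when they decide, refusal can depend on it, and replacement then changes one arm selectively.
2. **The distance rule.** It is phrased as a limit on control schools, given where the intervention schools are. If it is enforced after allocation by swapping controls, it tends to move the control arm towards sparser areas and leaves the intervention arm as drawn.
3. **Pupil level.** Baseline comes after allocation and, in the described order, after teacher training. Consent, attendance at baseline and baseline answers can therefore be influenced by knowledge of the arm. Timing of outcome-measurement also allows a teacher to assist with the questionnaire.

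The fallback randomisation adds a fourth, smaller opening: a first allocation might be looked at and then discarded.

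With four schools per arm there is little to dilute any of this, and the planned p-value takes the arms as randomised.

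**Working it through.** **Inputs from Sample size and power:** 4 schools per arm, 50 pupils per school, ICC 0.01–0.05, target difference 0.37–0.56 SD, two-sided 5%, 85% power.

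**The plan's own figures reproduce.** Design effect = 1 + (50 − 1) × ICC = 1.49 at ICC 0.01 and 3.45 at ICC 0.05 (stated: 1.5 and 3.5). Effective n per arm = 200/1.49 = 134.2 and 200/3.45 = 58.0. Detectable difference = (1.960 + 1.036) × √(2/n) = 0.366 and 0.557 (stated: 0.37 and 0.56). So 0.37 belongs to ICC 0.01 and 0.56 to ICC 0.05. The calculation takes all eight schools as randomised; the present point does not change it.

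**One substitution.** Share of an arm = 1/4 = 25%. Assume that the substitute differs from the refuser by one between-school SD, √ICC in units of the total SD. Shift in the arm mean = √ICC/4.

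| ICC | √ICC | Shift (SD) | Matched target | Share of target |
|---|---|---|---|---|
| 0.01 | 0.100 | 0.025 | 0.37 | 7% |
| 0.05 | 0.224 | 0.056 | 0.56 | 10% |

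**Refusal that depends on arm (illustration, no true effect).** Assume that only intervention schools with a below-average school effect refuse, each with probability r, and that substitutes follow the same rule. The expected bias is √(2/π) × √ICC × r/(2 − r). At ICC 0.05 and r = 0.5 this is 0.798 × 0.224 × 0.333 = 0.06 SD. Simulation (40,000 runs, t-test on school means, 6 df) agrees:

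| r | Bias, ICC 0.01 | Type I error | Bias, ICC 0.05 | Type I error |
|---|---|---|---|---|
| 0.2 | 0.01 | 4.9% | 0.02 | 5.3% |
| 0.5 | 0.03 | 5.5% | 0.06 | 6.1% |
| 1.0 | 0.08 | 9.0% | 0.18 | 14.7% |

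With the same refusal in both arms (r = 0.5 in each), bias is about 0 and type I error is 5.1% (ICC 0.01) and 5.0% (ICC 0.05).

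**The 5-km rule if enforced after allocation (illustration).** The article gives neither the number of eligible schools nor the area. The simulation assumed 40 or 100 schools in a square of side 20, 30 or 40 km, spread evenly or with a third of them around one town (1,500 runs each). At least one of the four control schools lay within 5 km of an intervention school in 50–96% of allocations, with a mean of 0.6–2.3 controls affected. After replacement, control schools had fewer neighbouring schools within 5 km than intervention schools in all twelve scenarios. The gap was small with an even spread (2.6 against 2.9 for 40 schools, 30 km) and larger with a town (3.2 against 5.3).

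**The case against.** The strongest reply is that much of this is inferred from the order of sentences. The text ties assignment to selection, but no word ties invitation to assignment. Principals are briefed about the study, not expressly about their arm. Sealed envelopes fit opening after agreement, and the two trial figures are not available here. All this stands: envelopes opened only after agreement would remove the refusal problem. They would not settle the distance rule or the timing of baseline.

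A reader might go further than the text in four places.

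- **That the substitute inherits the refuser's arm.** The article does not say so. It leaves both the draw and the arm open.
- **That the distance rule cannot work at selection, when no school has an arm.** It can, if all eight schools are chosen more than 5 km apart. The difficulty is that the rule is not worded that way.
- **That the shift could reach 15% of the target.** That divides the ICC 0.05 shift (0.056) by the ICC 0.01 target (0.37). Matched pairs give 7–10%.
- **That the analysis can do nothing.** Plan of analysis foresees adjustment for confounders fixed in advance, which may reduce bias. With eight schools it has little room, and it cannot restore randomisation.

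It is also fair that refusal may be rare. These are public schools, the Department of Education collaborates, local stakeholders are engaged to keep refusals low, and controls receive the programme later. At moderate selective refusal (r = 0.5) the simulated type I error rises only to 5.5–6.1%; 14.7% needs every below-average intervention school to refuse. On pupils, baseline precedes delivery, and children without consent may still attend sessions, so consent is not the price of the intervention.

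These points limit the likely size. They do not change the order in which the procedure is written.

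**Conclusion.** The point holds in this form: followed as written, the procedure does not protect the comparison as randomised. It allows replacement after arms are known and is silent on how substitutes are drawn and allocated. It directs the distance rule at control schools, and it describes baseline after intervention teachers have been trained in an open-label trial.

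A reader might conclude that the arms are no longer a randomised comparison. The document does not support that. Randomisation is lost only for schools replaced or removed after allocation. If no school refuses or breaches 5 km, the school-level comparison stays randomised, and refusal unrelated to arm produces no bias.

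On size, one substitution is a quarter of an arm, and a difference of one between-school SD moves the arm mean by 0.025–0.056 SD, or 7–10% of the matching target. The one-SD difference, the refusal probabilities and the geography in the simulations are assumptions; the real refusal rate and bias cannot be derived from the article. The case for acting rests on four schools per arm, on a fault that cannot be undone after allocation, and on a repair that needs only reordering.

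**What to change.** Rewrite Randomisation, Student-recruitment and Intervention-schools so that the steps run in this order.

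1. Put the eligible schools in a pre-specified random order. Invite from the top, and obtain each principal's written agreement to either arm. Take replacements for refusers as the next schools in that order.
2. At the same stage, require every pair of agreeing schools to be more than 5 km apart, whichever arm each may receive.
3. Obtain parental consent and pupil assent, and complete baseline in all eight schools.
4. Open the allocation once for all eight schools, 4 against 4. Fix in advance whether it is simple or covariate-constrained, so that no allocation is inspected and redrawn.
5. Train the intervention teachers.
6. Replace no school after allocation. A school that withdraws stays in its arm for the intention-to-treat analysis.

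The sample size remains 400 and the power calculation is untouched. According to Trial status and review, recruitment was expected only after March 2022, so this is a wording change if made before then. There are two costs. Teacher training starts slightly later, after baseline. The all-pairs distance rule narrows the choice of schools, towards more widely spaced ones in both arms alike; whether eight such schools exist should be checked on the eligible list first.

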#### Plan of analysis

The study tools/measures will be examined for internal consistency. Demographic and baseline characteristics will be summarised using descriptive statistics. Principal-analyses will be intention-to-treat which will take into account clustering by the school and repeated measures. To assess the effectiveness of interventions, outcomes will be compared between two trial arms using linear-mixed-model analysis for continuous outcomes and generalised linear mixed models or generalised estimating evaluation (GEE) for binary outcomes. The analysis will include all participants with at least one outcome measurement at 6 weeks post-intervention. A per-protocol analysis will also be conducted along with intention-to-treat analysis to examine the influence of missing data patterns. Multiple imputation will be attempted for missing values. The analysis will be adjusted for potential confounders that are identified a-priori during the study. Subgroup analysis will be performed for important socio-demographic variables. Statistical significance will be set at *p*-value< 0.05, and Bonferroni’s correction will be made for multiple testing (if any).

For qualitative analysis, all the verbatims of interviews/group discussions will be transcribed and translated into English for thematic analysis.

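### A school that refuses may be replaced after arms are assigned, so a school not randomised to an arm can enter it; agreement should come before a single allocation

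*Protocol article*

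**What the plan says.** The Randomisation section of the protocol article gives the steps in this order.

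1. Selection: "eight schools will be *randomly selected* using computer-generated random-number by an independent researcher".
2. Allocation: "The selected schools will then be assigned to the intervention, and waitlist-control condition". The same researcher does this from a random sequence. Schools carry study numbers that this researcher does not know, and "The sequence will be delivered through sealed, opaque envelopes".
3. Invitation, which opens the next paragraph: "The selected-schools will be invited to participate in the study, and briefing-meetings will be conducted to inform principals of selected-schools regarding the study".
4. Replacement: "In case of refusal, the refusing school will be replaced with another school from the eligible school-list".
5. Separation, to limit contamination: "no control-schools will be selected within 5 km radius of intervention-schools".

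The section does not state when the envelopes are opened relative to a school's agreement, whether a replacement is drawn at random, or whether allocation is repeated. The Plan of analysis section says "Principal-analyses will be intention-to-treat" and does not mention a school that is assigned and then refuses. Sample size and power fixes four schools per arm. Blinding describes the trial as open-label.

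**The concern.** On the written order, a refusal comes after assignment. With four schools per arm fixed, it leaves a vacancy in one particular arm. If that arm is already known, whoever fills the vacancy chooses a school for that arm, and the new school decides whether to join knowing what it will receive. Neither step is protected by the random sequence.

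The two arms ask for different things. Under Intervention-schools, teachers attend a three-day workshop, 10 to 15 hours of lessons are given over two months, and boosters follow. Table 2 adds audio-recording of sessions. Under Control-schools, teaching carries on unchanged until after the 12-month assessment. It is therefore plausible, though the documents give no figure, that schools would decline the intervention arm more readily. Replacement would then tilt that arm towards schools keen to deliver SUMS, while the control arm stayed closer to the random draw. That is selection bias in the randomised unit, and one school is a quarter of an arm.

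**Working it through.** **Order of steps.** Two features of the section bear on whether arms are known when a replacement is chosen.

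- Assignment is linked to selection by the word *then*. Invitation and refusal appear only afterwards.
- The 5 km rule makes the selection of a control school depend on where the intervention schools are. It can be applied only when arms are known, which does not fit a selection completed before assignment.

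Against these stands the sealed-envelope sentence, which gives no opening time. The concealment that is spelled out hides the identity of schools from the researcher who holds the sequence. It does not say that the arm is hidden from the schools or from the team that invites them.

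**The plan's own figures.** Inputs from Sample size and power: 4 schools per arm, 50 students per school (200 per arm), ICC 0.01 to 0.05, two-sided 5% level, 85% power.

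- Design effect = 1 + 49 × ICC = 1.49 and 3.45 (stated 1.5 and 3.5).
- SE of the standardised difference = √(2 × design effect / 200) = 0.122 and 0.186.
- Detectable difference = (1.960 + 1.036) × SE = 0.366 and 0.557 (stated 0.37 and 0.56).

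These reproduce. The point concerns the validity of the comparison, not the sample size.

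**Illustration of size.** Assumption, not in the documents: each replacement differs systematically from the refuser by one between-school SD, which is √ICC in units of the total SD (0.100 at ICC 0.01, 0.224 at ICC 0.05). With r of the four schools in one arm replaced:

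- bias B = r × √ICC / 4
- shift δ = B / SE
- type I error = Φ(−1.96 + δ) + Φ(−1.96 − δ)

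| ICC | r | B (SD) | δ | Type I error |
|---|---|---|---|---|
| 0.01 | 1 | 0.025 | 0.205 | 5.5% |
| 0.01 | 2 | 0.050 | 0.410 | 6.9% |
| 0.05 | 1 | 0.056 | 0.301 | 6.0% |
| 0.05 | 2 | 0.112 | 0.602 | 9.2% |

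Against the detectable difference, one replacement is 0.025/0.37 = 7% to 0.056/0.56 = 10%. Two are 0.050/0.37 = 14% to 0.112/0.56 = 20%.

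**Sensitivity to the assumed gap.** With a fixed gap of 0.2 to 0.5 SD instead, one replacement gives a bias of 0.05 to 0.125 SD. The type I error is then 6.9% to 17.6% at ICC 0.01 and 5.8% to 10.3% at ICC 0.05. The upper end is extreme: 0.5 SD is 5 between-school SDs at ICC 0.01 (0.5/0.100) and 2.2 at ICC 0.05 (0.5/0.224). The result follows the assumed gap, so the numbers show scale only.

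**The case against.** The best defence is that the section also describes concealment. If envelopes stay sealed until a school agrees, and a replacement takes over the refuser's study number, the replacement is validly randomised and no harm follows. The invitation paragraph speaks of selected schools, not allocated ones, so its place on the page may not be its place in time. A condensed article may also leave these details to the full protocol. This stands as a possibility, and it is why the point is conditional. It does not remove the point: the article states a sequence and a replacement rule, and the sequence and the 5 km rule both suggest that arms are known.

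Refusal may also be rare. These are public schools, the Department of Education collaborates, teachers are nominated by their superiors, stakeholders are to be engaged to limit refusals, and control schools receive SUMS later. That lowers the chance of harm. Even so, the protocol expects enough refusal to write a rule for it.

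The size can be challenged too. Two schools from the same list differ by chance, and the design effect already carries that variation. Only a systematic difference related to arm is bias, and the documents give no figure for one. This is correct.

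A reader might go further and infer that:

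- *the trial is no longer randomised or intention-to-treat.* This would hold only if a school refuses after its arm is known, and only for the replaced school;
- *replacements are picked non-randomly, and refusers vanish from the analysis.* The text is silent on both;
- *no analysis could help.* Baseline measurement and adjustment are planned, and a sensitivity analysis without replaced schools is possible. With four schools per arm these are weak, but they could reveal a problem.

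**Conclusion.** The point holds conditionally. As written, the procedure allows a school to enter a known arm without being randomised to it, and nothing in the article rules this out. Bias needs three things: a school refuses, its arm is known by then, and the refusal or the choice of replacement is related to arm or outcome. Under the assumed gap of one between-school SD, a single replacement does modest harm and two in one arm do more; the working gives the figures, which rest on the plan's ICC range and a normal test. They are not an estimate of what will happen. Because replacement after allocation cannot be reliably repaired with four schools per arm, and prevention costs little, this should be fixed before recruitment.

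**What to change.** Rewrite the Randomisation section so that agreement precedes allocation.

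1. The independent researcher draws a random ordered list of all eligible schools.
2. Schools are invited in that order. Each principal agrees in writing to either arm, and each refusal is met by the next school on the list.
3. The 5 km separation is settled among the agreeing schools before allocation, for example by accepting a school only if it lies at least 5 km from those already accepted.
4. When eight schools have agreed, all eight are allocated once.
5. Replacement after allocation is deleted. A school that withdraws later stays in its assigned arm for the intention-to-treat analysis, its student surveys are still sought, and its withdrawal is reported.

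The cost is protocol wording and a change in the order of steps. Trial status and review places recruitment after March 2022, so the article describes a trial that has not started. Eight schools, 400 students and the detectable difference of 0.37 to 0.56 SD are unchanged. Two modest costs remain. The trial will represent schools willing to accept either arm, so the number refusing before allocation should be reported. Step 3 may also use up the list faster; the text at hand does not give the number of eligible schools.

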### Study setting

The Department of Education in Karnataka state has three levels of schools viz., Primary (1–5 grades), Higher-Primary (6–8 grades) and High-schools (9–10 grades). The study will be conducted in higher-primary public schools in Srinivaspura taluka of Kolar District, Karnataka. Higher-primary public schools usually include children from ages 13 to 15 years. These grades were chosen because this is the period where life skills curriculum were introduced and this period in the life span also represents the point of departure for the rapid increase in psychiatric diagnoses that occurs prior to age 25 years [24].

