##### Sample size and power

Positive mental health literacy measured using the 10-item Mental Health-Promoting Knowledge (MHPK-10) scale is considered primary outcome for the present study [26]. However, the Intra-Cluster Correlation for MHPK-10 score is unknown. Based on evidence from similar adolescents studies, we assumed a conservative and modest estimate of ICC (ρ) between 0.01 and 0.05 [34, 35]. From the Kolar District Report (as on 30/3/2016), an estimated average of 50 students is expected from grade-6 and 7 of each higher-primary schools. With a need for 4 schools per arm with 50 students per school, we powered the trial to be able to detect a standardised difference (difference in means/SD) of 0.37–0.56 (medium effect size) for MHPK-10 scores between intervention and control groups for a two-sided level of significance at 5% (*α* = 0.05) with 85% power. For the above assumption, the design effect varied from 1.5 to 3.5 for ICC (ρ) values from 0.01 to 0.05, respectively [36]. We expect a minimum sample size of 400 across 8 schools for 85% power. Even with a 5% loss to follow-up, the study will still have more than 80% power.

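### The 5 km separation rule conflicts with the stated random draw and simple randomisation, and its control-only wording leaves room for control schools to be swapped after allocation

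*Protocol article*

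**What the plan says.** All the relevant text is in the protocol article, mainly under Randomisation.

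- **Draw.** "eight schools will be *randomly selected* using computer-generated random-number by an independent researcher". No distance condition is attached.
- **Allocation.** "The selected schools will then be assigned to the intervention, and waitlist-control condition", through a random-allocation sequence that the same section later calls simple randomisation.
- **Concealment.** "randomly selected schools will be assigned unique study numbers that will not be known to the independent researcher at the central office".
- **Replacement.** "In case of refusal, the refusing school will be replaced with another school from the eligible school-list". No other reason for replacement is given.
- **Separation.** "no control-schools will be selected within 5 km radius of intervention-schools", as a safeguard against contamination.
- **Restricted randomisation.** "An alternate covariate-constrained randomisation will be considered only if we do not reach an acceptable baseline balance through simple-randomisation". This fallback is for baseline balance and does not mention distance.

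Two other sections set the scale. Study setting places the trial in one sub-district: "The study will be conducted in higher-primary public schools in Srinivaspura taluka of Kolar District, Karnataka". Sample size and power fixes the number of clusters: "With a need for 4 schools per arm with 50 students per school".

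**The concern.** The separation rule is written in terms of arms, and arms exist only after allocation. It also restricts control schools only. Nothing in the draw or the allocation sequence enforces it, so a school allocated to control may turn out to lie within 5 km of an intervention school. The document does not say what happens then, who checks, or when.

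The wording most readily suggests replacing the offending control school with one further away. That would be a change to one arm made after allocation is known. Intervention schools would remain a random draw, while control schools would be a random draw filtered for distance from them. Remoteness and whatever travels with it could then differ systematically between arms. With four schools per arm, one replacement is 25% of the control arm, and eight clusters give little scope to adjust the difference away.

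**Working it through.** **1. The plan's own figures.** The inputs, from Sample size and power, are 4 schools of 50 per arm (200 per arm), ICC 0.01 to 0.05, two-sided 5% and 85% power.

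- Design effect = 1 + (50 − 1) × ICC, which is 1.49 at ICC 0.01 and 3.45 at ICC 0.05 (stated as 1.5 and 3.5).
- Detectable difference = (1.960 + 1.036) × √(2 × design effect / 200), which is 0.366 and 0.557 (stated as 0.37 and 0.56).

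These reproduce, and the sample size is not affected by this point. They matter below because 0.37 belongs to ICC 0.01 and 0.56 to ICC 0.05.

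**2. Can the stated procedure deliver the rule?** Only if the eight drawn schools and their split happen to comply. The draw ignores distance, simple randomisation ignores distance, and both the replacement step and the constrained-randomisation fallback are tied to other triggers.

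**3. How often would a random split breach the rule?** The document gives no area, list size or school locations, so these are assumed: schools spread evenly over a square of side L. The chance that two random schools lie within 5 km is p = πr² − (8/3)r³ + r⁴/2, with r = 5/L. There are 4 × 4 = 16 intervention-control pairs. Treating pairs as independent, P(breach) ≈ 1 − (1 − p)^16, and the expected number of control schools in breach ≈ 4 × [1 − (1 − p)^4].

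| Assumed area (km²) | p | P(breach), formula | P(breach), simulated | Control schools in breach |
|---|---|---|---|---|
| 500 | 0.128 | 89% | 88% | 1.7 |
| 800 | 0.084 | 75% | 75% | 1.2 |
| 1000 | 0.068 | 68% | 67% | 1.0 |
| 1500 | 0.047 | 53% | 53% | 0.7 |

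The simulated column uses 40,000 random draws per area. A second set of assumptions (squares of side 20, 30 or 40 km; 30 or 80 schools; evenly spread or with 40% around one town) gives breaches in 50% to 98% of draws.

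**4. What would replacing control schools do?** It depends on how schools are laid out.

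- *Evenly spread:* little. The mean number of listed schools within 5 km is 4.5 (intervention) against 3.7 (control) for a 20 km side and 30 schools, and 3.4 against 3.3 for a 40 km side and 80 schools.
- *Town cluster (assumed: 60 schools, 40% around one town with a 3 km spread):* about 40% town schools in the intervention arm and 21% in the control arm, a difference of 0.19.

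**5. How large could the bias be?** Bias = 0.19 × d, where d is the town-remote gap in MHPK-10 in SD units. The document gives no d, but its ICC range caps it. A gap d between 40% town and 60% remote schools contributes 0.4 × 0.6 × d² = 0.24d² to between-school variance, and this cannot exceed the ICC on the SD scale.

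| ICC | Cap on d = √(ICC/0.24) | Bias = 0.19 × d | Matching detectable difference | Share |
|---|---|---|---|---|
| 0.01 | 0.20 | 0.04 | 0.37 | 10% |
| 0.05 | 0.46 | 0.09 | 0.56 | 15% |

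These are upper limits for this layout, because they attribute all between-school variance to town against remote.

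**The case against.** The strongest reply is that the document never says a control school is swapped for distance. A reader might infer from the wording that the rule can act only once arms are known, and so that the arms are not a random split. The text does not support that:

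- The section uses one verb for drawing schools from the list and another for allocating them, so the rule can be read as a condition on the draw.
- Spacing all eight schools before allocation would satisfy the rule and keep the arms exchangeable. So would randomising only among splits that comply.
- Redrawing the split of the same eight schools until it complies does not filter controls either. Distance is symmetric, and under the town-cluster assumption this route gave the same town share (0.34 to 0.36) in both arms.
- Masked study numbers do not rule out a distance check. They are hidden from the researcher at the central office, but someone else could check the eight schools before the envelopes are opened.

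A larger bias is also tempting: a 0.5 SD gap gives 0.19 × 0.5 = 0.095 SD, about 25% of 0.37. That pairs incompatible assumptions. A 0.5 SD gap implies between-school variance of 0.24 × 0.25 = 0.06, above the protocol's ICC ceiling of 0.05, while 0.37 belongs to ICC 0.01. The calculation also leaves out the baseline measurement and the planned adjustment for confounders.

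All of this stands, and it limits the claim. It does not remove the conflict. The benign routes are possible but not stated, and a rule that the described procedure cannot guarantee is more than detail left to a fuller document.

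**Conclusion.** The point holds as a conflict between a stated rule and a stated procedure. Random selection followed by simple randomisation cannot guarantee that control schools lie at least 5 km from intervention schools, and no step is given for a breach. Under the assumed areas a breach would occur in about half of draws or more, so the question is likely to arise in practice.

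Whether bias follows depends on how the breach is resolved. It follows if control schools are replaced after allocation. It does not follow if the first draw complies, or if separation is settled before allocation. The size cannot be computed from the document. The range of 0.04 to 0.09 SD is an upper limit under one assumed town-cluster layout; with evenly spread schools replacement makes the arms differ much less in remoteness. The case for correction rests on protecting the randomised comparison, not on those figures.

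**What to change.** State in the Randomisation section that the 5 km condition is applied before allocation, by one of two routes:

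1. Draw schools from the list in random order, skip any school within 5 km of one already drawn, stop at eight, and then allocate; or
2. Draw eight schools and randomise only among the 4:4 splits that meet the between-arm rule.

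Add two sentences: that no school is dropped, swapped or replaced for distance after allocation; and that any replacement for refusal meets the same condition before arms are revealed.

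The cost is protocol wording and a distance check on a school list that the plan already requires. Route 1 is stricter than the current between-arm rule and makes the sample somewhat more dispersed. Route 2 reduces the set of allowable allocations, and some draws of eight may have no compliant split, so the text should say that the draw is then repeated before any allocation. Treating neighbouring schools as one allocation unit is not a cheap alternative, because it leaves fewer than eight units in a trial that has only eight. Trial status and review anticipates recruitment only after March 2022, so on that timetable the change could be made before any school is allocated.
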